### Sample Size Estimation

An estimated sample size of 2389 participants was determined to achieve 80% power at a type I error of 5%, adjusted for multiple comparisons using the Bonferroni correction. Four comparisons were considered according to the study objectives; therefore, the adjusted level of significance is 1.25%, with a corresponding 2-tailed Z value of 2.238. We also adjusted for a 24% LTFU among patients with TB, based on findings from the formative study that informed the design of these interventions. We assumed a 40% reduction in LTFU based on previous similar studies [36,37] for comparisons between SOC and either SMS reminders alone or telephone calls alone, resulting in an assumed proportion of LTFU of 14.4% in both these groups. For comparisons between SOC and combined interventions (SMS reminders or telephone calls with a transport incentive), a 50% reduction will be considered clinically significant, given the expected higher impact of the incentive. The sample size has been further adjusted for clustering using a design effect of 1.5 to account for the clustering anticipated at the health facility level and a postenrollment attrition rate of 20%.

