### Data Management and Analysis

#### Overview

ODK data will be downloaded into Microsoft Excel and transferred to Stata 14 (StataCorp LLC) for cleaning and analysis. The primary analytical approach will follow the intention-to-treat principle, with participants in the intervention arm considered exposed to the intervention regardless of whether they received specific intervention services. We will assess for any contamination by conducting and comparing the results of the intention-to-treat and per-protocol analyses. Descriptive statistics (means, medians, and proportions) will be used to describe participant characteristics across the study arms. We will control for characteristics that are not balanced across the study arms in the fitted regression models. Chi-square tests will be performed for categorical outcomes. Log-binomial regression models using generalized linear modeling will be applied to assess associations between each intervention and the outcomes. A *P* value <.05 will be considered statistically significant.

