#### Interim Analysis

Although this trial does not pose a significant risk to participants, we plan to conduct an interim analysis. Findings from the interim analysis will be shared with the data and safety monitoring board (DSMB) to determine whether the trial should continue based on the emerging results.

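### The sample size promises a 5% error over four comparisons by Bonferroni (1.25% each), but the only threshold in the analysis section is an unadjusted P<.05

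*Protocol article*

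**What the plan says.** In the protocol article, Sample Size Estimation sets the overall error at 5%, "adjusted for multiple comparisons using the Bonferroni correction". It continues: "Four comparisons were considered according to the study objectives", and concludes that "the adjusted level of significance is 1.25%, with a corresponding 2-tailed Z value of 2.238". The comparisons it describes are SOC against each of the four intervention arms.

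Under Data Management and Analysis, the Overview describes chi-square tests and log-binomial models that "will be applied to assess associations between each intervention and the outcomes". The next sentence gives the decision rule: a P "value <.05 will be considered statistically significant". No other section of the article gives a significance threshold for the analysis, and the 1.25% level does not appear again after the sample size section.

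**The concern.** The design claims error control over a family of four tests, but the analysis rule as worded tests each of them at the full 5%. An analyst who follows the Overview would call an arm significant at P = .03. The Bonferroni level in the sample size section would not.

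The difference matters because Objectives and Hypothesis expects a benefit from every intervention, so each arm can produce its own positive claim, and the Conclusions expect the trial to inform practice and policy. The Results section reports 2355 participants recruited by 28 August 2025 and preliminary analyses under way. If the rule is settled only after the P values are known, the choice between .0125 and .05 is open to influence from the results.

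**Working it through.** **Inputs from the protocol article.** Overall error 5%, four comparisons, Z = 2.238, 80% power, design effect 1.5, attrition 20%, N = 2389 (Sample Size Estimation). Prediagnosis loss to follow-up 24% under SOC, 14.4% with a single intervention, 12% with a combined one (Objectives and Hypothesis). Allocation 2:2:2:1:1 (Randomization and Blinding).

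**1. Reproduce the plan's figures.** The per-comparison level is 0.05/4 = 0.0125, as stated. For 24% against 14.4%, the pooled two-proportion formula is

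n = [Z√(2p̄(1−p̄)) + z_β√(p₁(1−p₁) + p₂(1−p₂))]² / (p₁−p₂)²

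With p̄ = 0.192, Z = 2.238 and z_β = 0.8416:

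n = [2.238√0.3103 + 0.8416√0.3057]² / 0.096² = 318 per full-size arm.

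Inflating, 318 × 1.5/0.80 = 596.25, rounded up to 597. The half-size arms have 299. The total is 3 × 597 + 2 × 299 = 2389, which matches exactly.

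**2. Family-wise error under the global null.** The four test statistics share the SOC arm. With r the size of an intervention arm relative to SOC, the statistic loads on the shared control with λ = √(r/(r+1)). This is √(1/2) for the two single-intervention arms and √(1/3) for the two combined arms. For critical value c,

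FWER = 1 − ∫ ∏ᵢ [Φ((c−λᵢx)/√(1−λᵢ²)) − Φ((−c−λᵢx)/√(1−λᵢ²))] φ(x) dx

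For false claims of benefit only, the second Φ term is dropped.

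| Per-test rule | c | Any false positive, either direction | At least one arm falsely better than SOC |
|---|---|---|---|
| P<.05, as the Overview says | 1.960 | 16.4% | 8.2% |
| Z used for sizing | 2.238 | 8.7% | 4.4% |
| Two-sided P<.0125 | 2.498 | 4.5% | 2.3% |

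A binomial simulation with 24% loss in every arm gave 16.4% to 16.5% for the first row. If the tests were independent, the two-sided figures would be 1 − 0.95⁴ = 18.5% and 1 − 0.9875⁴ = 4.9%.

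**3. What the sizing Z stands for.** The two-tailed value for 1.25% is 2.498. A Z of 2.238 has a two-sided P of about .025, and is close to the one-sided 1.25% value of 2.241. Because N = 2389 was built on 2.238, it does not provide 80% power at two-sided .0125.

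**4. Power with N = 2389.** The effective arm sizes are 597 × 0.80/1.5 = 318.4 and 299 × 0.80/1.5 = 159.5.

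| Comparison with SOC | Z = 2.238 | Z = 2.498 |
|---|---|---|
| Single intervention, 24% v 14.4% | 80% | 72% |
| Combined intervention, 24% v 12% | 83% | 74% |

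At Z = 2.498 the formula in step 1 gives 375 per full-size arm, hence 375 × 1.5/0.80 = 703.1, rounded up to 704, and a total of 3 × 704 + 2 × 352 = 2816.

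**The case against.** The best defence is that the P<.05 sentence closes a condensed overview that also covers secondary outcomes, and that P<.05 applied to Bonferroni-adjusted P values is the same as 1.25% per test. On that reading the two sections agree. The reading is possible, but the text does not say it. The sentence directly follows the models for each intervention on the outcomes and carries no qualification. An unseen analysis plan does not settle the matter either, since the article itself states both the 1.25% level and the .05 rule. What stands of this defence is that one clarifying clause would remove the conflict, so it is too strong to say that the two sections can under no reading both hold.

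Two stronger readings should be resisted. A reader might infer a 1 in 6 chance of declaring a useless intervention effective. The 16.4% counts differences in either direction, including an arm found worse than SOC; false claims of benefit come to 8.2%, about 1 in 12.

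A reader might also infer further inflation from the interim analysis, whose findings go to the monitoring board "to determine whether the trial should continue based on the emerging results". The Interim Analysis section gives no threshold, efficacy boundary or timing, and nothing says that .05 applies there. Such rules are commonly left to an analysis plan or board charter. No interim inflation can be calculated from this document, and none is claimed.

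**Conclusion.** The point holds for the four primary comparisons with SOC. As worded, the Overview's rule does not deliver the 5% error stated in the sample size section: it gives 16.4% two-sided, about 3.6 times the 4.5% at two-sided P<.0125 (16.4/4.5). The ratio is the same for false benefit alone (8.2/2.3).

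These figures assume that no intervention has any effect, that the test statistics are approximately normal, and that allocation is 2:2:2:1:1 with one shared control. They cover the primary outcome at a single final analysis. Even if the sizing Z of 2.238 is taken as the intended cut-off, the family-wise error is 8.7%, so no reading of the sample size section supports an unadjusted .05. The power figures also rest on the plan's own loss-to-follow-up assumptions, design effect and attrition.

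**What to change.** Amend the Overview to say that, for the primary outcome, each of the four comparisons with SOC is tested at two-sided P<.0125 (equivalently, Bonferroni-adjusted P<.05) and reported with a 98.75% confidence interval. Add that P<.05 without adjustment applies only to secondary outcomes, which are not confirmatory.

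Holm at a family-wise 5% would be an acceptable alternative. It tests successive ordered P values against .0125, .0167, .025 and .05, so 98.75% intervals would not always agree with its decisions, and the text should say so.

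Correct the Z value in Sample Size Estimation at the same time, and restate the power with 2389 participants as about 72% for single interventions and 74% for combined arms.

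The wording costs a few sentences and should be fixed before anyone sees results by arm. The real costs are that, under the Bonferroni rule, primary results with P between .0125 and .05 lose the label significant, and that the trial is acknowledged to have less than 80% power at its own stated level. With recruitment nearly complete, reaching 80% at that level would take about 2816 participants, 427 more than the planned 2389.

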#### Interim Analysis

Although this trial does not pose a significant risk to participants, we plan to conduct an interim analysis. Findings from the interim analysis will be shared with the data and safety monitoring board (DSMB) to determine whether the trial should continue based on the emerging results.

### Ethical Considerations

The study was approved by the Makerere University School of Public Health Research and Ethics Committee (799) and the Uganda National Council of Science and Technology (HS993ES). The study will be conducted in accordance with the World Medical Association Declaration of Helsinki. Written informed consent will be obtained from all participants. Each participant will receive compensation of 10,000 Ugandan shillings (US $3) only for their time in the study at each level of data collection. All hard-copy study materials will be stored securely under lock and key, with access restricted to core project staff. Electronic data will be stored on a password-protected server hosted at Verton IT Ltd, with access similarly restricted to core project staff. To minimize the risk of inadvertent disclosure of presumptive TB status through SMS reminders or telephone calls received by unintended recipients, we will ensure that the SMS reminder content is neutral, with no mention of the word “TB,” serving only as a reminder to the patient to return to the health facility. This approach was adopted based on feedback from the co-design workshop with stakeholders, who recommended avoiding the use of the word “TB” in the SMS reminder content. We will also only recruit participants who personally own a mobile phone and do not share it with others. Furthermore, at the beginning of each telephone call, participants will be asked to identify themselves to confirm that the data collectors are speaking with the correct individual. All enrolled participants will be assigned a unique ID number at recruitment, which will be used throughout the study period. All data will be deidentified before analysis. The trial has been registered at ClinicalTrials.gov (NCT05964842).

### Study Oversight and Monitoring

The study investigators, coordinator, supervisors, and research assistants will meet daily during participant recruitment for quality control purposes. This trial will be monitored by an independent DSMB and a local steering committee (LSC). The DSMB will serve as the core technical team responsible for reviewing cumulative trial data, monitoring adherence to the trial protocol, and ensuring patient safety. It will also review any suggestions for protocol amendments. The DSMB will comprise 3 members (an epidemiologist, a clinical officer, and a senior researcher) and meet every 2 months to assess trial progress. The LSC will provide administrative oversight, ensuring adherence to study procedures, monitoring trial progress, and providing advice and guidance. It will comprise 7 members (a community advisory member, an IT specialist, 2 policymakers, a biostatistician, an epidemiologist, and a social worker) and meet every 6 months.

### Adverse Events Monitoring and Reporting

The planned trial interventions pose minimal risk to participants; hence, we do not anticipate serious adverse events. However, we will continually conduct risk assessments to identify any incidents that may occur. The research assistants will be trained to monitor for adverse events, document them accurately, and follow established reporting procedures. All adverse events occurring during the study, whether or not considered related to the study, will be reported in writing to the study team, the LSC, the DSMB, and the Makerere University School of Public Health Research and Ethics Committee for assessment and further review. Each event will be recorded in the study registry, documenting the following information: description of the event, date of occurrence, participant details, onset and end dates, and severity. We will actively follow up each event until resolution or stabilization.

### Dissemination Plan for Research Findings

All findings from the trial will be disseminated in workshops and conferences as oral or poster presentations. The target audience will include members of the Uganda National TB and Leprosy Program research forum, policymakers, TB program implementing partners, academic researchers, and the study participants. Policy briefs will be prepared, and a report of the study findings will be submitted to the participating health facilities and to the funder, the European and Developing Countries Clinical Trials Partnership. All findings will be published in open-access, peer-reviewed journals.

## Results

The study was funded in June 2020 and data collection for this RCT started in August 2023. We encountered delays during the COVID-19 period hence the RCT started at a later date than anticipated. The results are not yet available. Results from the preliminary analysis will be ready by December 2025. As of August 28, 2025, a total of 2355 participants had been recruited, and preliminary analyses are ongoing. The final results are expected to be published by March 2026.

## Discussion

### Summary

The MILEAGE4TB study is an individual randomized controlled trial to determine the effect of SMS reminders, telephone calls, and transport incentives on enhancing completion of TB diagnosis among persons with presumed TB and initiation of treatment for diagnosed patients. The study hypothesizes that, compared to SOC, each individual intervention—SMS reminders alone, telephone calls alone, or a combined intervention of either SMS reminders or telephone calls with transport incentives—will reduce prediagnosis LTFU. Some of the factors contributing to patient LTFU are high patient loads, cartridge shortages, and low staffing levels in laboratories [31,32]. In addition, evidence indicates that even with improved diagnostic tools such as Xpert MTB/RIF, same-day results are often not feasible in low- and middle-income countries (LMICs) due to the unavailability of Xpert MTB/RIF equipment and thus the need to refer specimens for testing. These delays prevent same-day result delivery, increasing the likelihood of patient LTFU.

This study will address cascading patient LTFU along the TB care continuum, particularly at 2 time points: before diagnosis and after treatment*.* Prediagnosis and pretreatment LTFU are important because untreated patients with TB remain infectious and can continue to transmit TB in the community, while failure to initiate treatment results in poor patient outcomes, including death [6,24,38]. Studies have shown that timely diagnosis and treatment improve patient outcomes [39,40]. Effective TB case detection has been reported to lower TB incidence, prevalence, and mortality levels [41]. Therefore, routine follow-up of patients during the process of diagnosis and linkage to treatment is important. This is in line with the targets of the “End TB Strategy” and the United Nations’ Sustainable Development Goals [42]. In addition, instances of pretreatment LTFU are not included in routine reporting by national TB programs, leading to an overestimation of program effectiveness [43].

The proposed intervention uses SMS reminders and telephone calls to improve communication between patients and health care providers, while transport incentives address the economic barriers associated with completion of TB diagnosis and treatment initiation. Telephone-based interventions such as SMS reminders and telephone calls have successfully improved adherence to TB treatment in Uganda [44-46] and increased the uptake of other health interventions, such as childhood immunization [47]. In addition, incentives have been found to improve health care outcomes [48-50]. However, there is limited data from LMICs on the role of SMS reminders, telephone calls, and transport incentives in interventions seeking to improve completion of TB diagnosis and initiation of treatment for diagnosed patients. This study will provide evidence on the use of mHealth strategies and incentives to improve completion of TB diagnosis and initiation of treatment for diagnosed patients.

Given that the phase of being presumed for TB offers an opportunity for early diagnosis and treatment initiation [51,52], this study, whose aim is to enhance completion of TB diagnosis and initiation of treatment for diagnosed patients, is critical to achieving the targets of the “End TB Strategy” [2]. In addition, our study will put into practice the “Find. Treat. All.” initiative, which seeks to close gaps in TB detection and treatment. This initiative, launched in 2018 by the WHO in collaboration with the Stop TB Partnership and the Global Fund to Fight AIDS and Tuberculosis, focuses on improving the quality of TB services through assessment of the TB care cascade and identification of missing cases [53]. Furthermore, the provision of transport incentives is in line with the principles of social protection for patients and supports the attainment of universal health coverage, as outlined in Sustainable Development Goal 3 and the “End TB Strategy” [42].

### Study Strengths and Limitations

This randomized controlled trial is expected to provide one of the highest levels of evidence for ways to enhance completion of the TB diagnostic process and treatment initiation. The study will be conducted across different levels of health facilities to enhance representativeness and increase the generalizability of the findings. In addition, we are implementing a multifaceted intervention comprising SMS reminders, telephone calls, and transport incentives, which is an approach that, to the best of our knowledge, has not been previously evaluated among persons with presumptive TB.

However, blinding will not be possible at all levels, particularly for participants, which may introduce some bias. This risk will be minimized through continual clarification of the study goal and methods. Moreover, individuals who share mobile phones will be excluded to avoid inadvertent disclosure of their testing status. This exclusion criterion may limit participation of certain populations that could have benefited from this intervention.

### Conclusions

This study will assess the effect of SMS reminders, telephone calls, and transport incentives on enhancing completion of TB diagnosis among persons with presumed TB and treatment initiation for diagnosed patients within Uganda’s health care system. The trial will provide evidence that can inform health care practice and policy related to the TB diagnosis process, which could ultimately improve patient care. The use of SMS reminders and telephone calls in the phase of being presumed for TB will provide insights on their effectiveness in this phase, which has not been extensively explored. Moreover, the application of these technologies will add to existing evidence on the effectiveness of mHealth in improving health service delivery.
